#### **9.4 Subgroup analyses**

We will conduct pre-planned subgroup analyses to investigate any differential effects according to baseline urine volume (a surrogate for residual kidney function), diabetic status, line, weight at baseline, age and the experience of sites in achieving high-volume HDF. Subgroup analyses will be conducted by including an interaction term between allocated treatment and baseline characteristic in regression models then using the likelihood ratio test comparing this model with one excluding the interaction term. Urine volume and age will be included in the model as continuous variables.

#### **9.5 Adjusted analysis**

All analyses will be adjusted for stratification variables and, in the case of patient-reported outcomes, we will also adjust for the value of the outcome pre-randomisation. For all statistical models used the underlying assumptions will be checked using standard methods. If assumptions are not valid then alternative methods of analysis will be sought.

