## STUDY PROTOCOL

### The High-volume Haemodiafiltration vs High-flux Haemodialysis Registry Trial

#### 1 BACKGROUND

End-stage kidney disease (ESKD) affects ~55,000 people in the UK, with ~7,000 newly affected people each year (1, 2). It ranks among the most severe of the chronic non-communicable diseases. The survival probability at one, three and five years is around 90, 70 and 50%, respectively (3). Morbidity is high, with dialysis patients in the UK admitted to hospital on average ~1.5-2.0 times per year and spending ~15 days in hospital per year (4). Quality of life on dialysis is also well below that of the general population (5). There is therefore an unmet and urgent need to improve ESKD patient treatment.

Renal replacement therapy (dialysis or transplantation) is necessary when approximately 90% of kidney function is lost. Currently ~90% of existing dialysis patients are on some form of haemodialysis (HD) or haemodiafiltration (HDF) (2). Although HD and HDF can be performed at home, the majority is performed in-centre.

HD relies on 'diffusion' – molecules at high concentrations in the blood pass across a membrane in an artificial kidney or dialyser to reach low concentrations in the dialysate fluid. At first, the pores in these membranes had to be small to avoid the loss of proteins and this meant that only small-sized toxic molecules could leave the blood. As technology advanced, these pores became larger and more complex/ asymmetrical, making it easier for larger toxic molecules to leave the blood whilst essential proteins are retained. These "high-flux" membranes are now recommended as standard practice in the UK (6). Even with these high-flux membranes, however, only the equivalent of 10-15% of toxin removal can be achieved within the timing/ frequency of a fairly standard dialysis prescription (i.e. 4 hours three times a week) (7).

HDF is similar to HD in that it uses diffusion to clean the blood (see above), but at the same time it uses 'convection' – a process that pulls fluid across the membrane, taking any dissolved solutes with it. When large volumes of fluids are pulled across the membrane (more than 23L per treatment session) it is considered 'high-volume' HDF. Adding convection achieves more efficient removal of middle-sized water soluble and even protein bound toxic molecules that cause cardiovascular damage, impaired immunity and other organ damage (8). This could explain why meta analyses of

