#### **4 TRIAL DESIGN**

A non-blinded, randomised, parallel group, controlled trial comparing high-volume HDF (aiming for 21+L of substitution fluid adjusted to body surface area) against high-flux HD, randomised 1:1 and stratified by site, age (18-64 and 65+) and residual renal function (urine volume <100mL/day and 100+mL/day (26-28)). The primary analysis will be intent to treat using proportional hazards regression and adjusting for variables used to stratify the randomisation.

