**Table 1 Summary of baseline data collection for the randomised controlled trial**

|                     |                                                                                                                                                                                                                                                                                                                             |
|---------------------|-----------------------------------------------------------------------------------------------------------------------------------------------------------------------------------------------------------------------------------------------------------------------------------------------------------------------------|
| Demographics/social | Age, sex, ethnicity, marital status, education level, smoking history.                                                                                                                                                                                                                                                      |
| Clinical            | Primary renal disease, date first seen by nephrologist, RRT treatment history, co-morbidities, dietary restrictions, prescribed medication (including erythropoiesis stimulating agents and phosphate binders), 24-hour urine volume (within the 6 weeks preceding randomisation).                                          |
| Resource use        | Day case and inpatient hospital admissions (including surgical procedures performed), nursing home/residential home days/hospice days, other hospital outpatient services and primary care & community services in the last 6 months.                                                                                       |
| Laboratory          | Creatinine, urea, Kt/V, urea reduction ratio, albumin, haemoglobin, haematocrit, mean corpuscular volume, sodium, potassium, bicarbonate, corrected calcium, phosphate, c-reactive protein, intact parathyroid hormone, total cholesterol. (From the date of the study visit or the closest date prior to the study visit.) |
| Physical assessment | Height, weight, blood pressure, heart rate.                                                                                                                                                                                                                                                                                 |

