#### **9.3.3 Secondary outcome analysis**

The secondary outcomes of all-cause mortality, non-cancer mortality, cardiovascular mortality, infection mortality will be analysed and reported in a similar manner to the primary outcome as described in section 9.3.2.

Cardiovascular and infection-related hospitalisations and MRSA and MSSA infections are all recurrent events and analyses of such outcomes should account for informative censoring due to death. We will therefore use joint frailty models (JFMs) as these simultaneously analyse recurrent events (infections or hospitalisations) and time to death while estimating distinct hazard ratios. Appropriate repeated measures regression models for patient-reported outcomes will be chosen based on the distribution of the data and will adjust for stratification variables and values of the outcome at the time of randomisation. A similar repeated measures regression approach will be taken to the following other repeated measure outcomes: time to recover after each dialysis session, haemoglobin levels, erythropoiesis stimulating agent dose, calcium levels, phosphate levels, PTH levels, albumin levels, and phosphate binder dose.

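### The models for recurrent cardiovascular and infection admissions leave out the pre-randomisation admission history collected at baseline, which costs some precision but causes no bias

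*Protocol*

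**What the plan says.** Section 9.3.3 states that "Cardiovascular and infection-related hospitalisations and MRSA and MSSA infections are all recurrent events", and gives the method: "We will therefore use joint frailty models (JFMs) as these simultaneously analyse recurrent events (infections or hospitalisations) and time to death". It names no baseline covariate for these models.

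Section 9.5 gives the general covariate rule: "All analyses will be adjusted for stratification variables". It then adds one further covariate for one class of outcome: "in the case of patient-reported outcomes, we will also adjust for the value of the outcome pre-randomisation". Section 4 lists the stratification factors: randomisation is "stratified by site, age (18-64 and 65+) and residual renal function". Admission history is not among them.

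Section 9.3.3 also says that haemoglobin, calcium, phosphate, PTH, albumin and the two drug doses will be handled much as the patient-reported outcomes are, and those are adjusted for their values at randomisation. The only other route to extra covariates is section 9.3.1, which allows additional adjustment in sensitivity analyses prompted by baseline imbalance.

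The baseline data in Table 1 include, under Resource use, "Day case and inpatient hospital admissions (including surgical procedures performed", in a row that ends with a 6-month look-back. Appendix 1 ticks the same item at baseline and again under linkage.

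**The concern.** Patients on dialysis differ widely in how often they are admitted, and that heterogeneity is a large part of the variance of a treatment effect on recurrent admissions. A frailty term allows for the heterogeneity but does not explain it, so it still enters the standard error. An observed predictor of a patient's admission rate removes part of it.

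Recent admissions are a natural predictor, and the trial already holds them. The protocol accepts the principle for patient-reported, laboratory and dose outcomes but does not carry it over to the hospitalisation models, which bear on the morbidity objective in section 3.2. An analyst who follows 9.3.3 and 9.5 as written would leave the covariate out. What is at stake is the width of the confidence intervals on these secondary outcomes.

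**Working it through.** **No plan figure to reproduce.** The sample size in section 9.1 concerns the time-to-first-event composite. The protocol states no power, effect size or variance for the recurrent outcomes.

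**Inputs from the protocol.** 1550 participants; follow-up 32 to 91 months; patients are "admitted to hospital on average ~1.5-2.0 times per year" (lower end, 1.5, used here).

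**Assumed inputs.** 30% of admissions are cardiovascular or infection; frailty variance k = 0.5, 1 or 2; correlation r between the propensity behind past all-cause admissions and that behind future cause-specific admissions = 1, 0.7 or 0.5.

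**Approximation by hand.** In a gamma-Poisson model, the variance of the log rate ratio is proportional to:

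- without the prior count: 1/μ + k
- with it: 1/μ + k(1 − r²q), where q = k·m0/(1 + k·m0)

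Here μ is the expected number of follow-up events and m0 the expected number of prior admissions in 6 months. At the minimum follow-up, μ = 1.5 × 0.30 × 32/12 = 1.20 and m0 = 1.5 × 0.5 = 0.75.

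For k = 1:

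- q = 0.75/1.75 = 0.429
- without the count: 0.833 + 1 = 1.833
- with it, r = 1: 0.833 + 0.571 = 1.405; ratio 0.766, a 23% reduction
- with it, r = 0.7: 0.833 + (1 − 0.49 × 0.429) = 1.623; ratio 0.885, a 12% reduction
- with it, r = 0.5: 0.833 + (1 − 0.25 × 0.429) = 1.726; ratio 0.942, a 6% reduction

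**Simulation.** 1550 patients, follow-up uniform on 32 to 91 months and cut short by frailty-linked death (hazard 0.119 × √frailty a year). A negative binomial rate model stands in for the recurrent part of the joint model. It is fitted with and without log(6-month prior admissions + 0.5). Reduction in the variance of the log rate ratio:

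| Correlation of past and future propensity | k = 0.5 | k = 1 | k = 2 |
|---|---|---|---|
| 1.0 (fully shared and constant) | 12% | 23% | 38% |
| 0.7 | 5% | 10% | 17% |
| 0.5 | 3% | 5% | 7% |
| 0.3 | 1% | 2% | 3% |

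At full sharing the median standard errors were 0.0574 to 0.0540 (k = 0.5), 0.0703 to 0.0618 (k = 1) and 0.0903 to 0.0713 (k = 2). For k = 1, (0.0618/0.0703)² = 0.773, which is the 23% in the table. The hand calculation agrees to within 2 percentage points at k = 0.5 and 1. At k = 2 it is a few points more favourable (for example 0.792, or 21%, against 17% at r = 0.7).

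**In practical terms.** A variance reduction of 3-17% makes intervals narrower by 1 − √0.97 = 1.5% up to 1 − √0.83 = 9%. That equals the information from 1/0.97 = 1.03 to 1/0.83 = 1.20 times as many participants.

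**Limits of the check.** The models omit site, age and urine volume, which the protocol adjusts for and which may already explain part of the heterogeneity. The negative binomial model is not a joint frailty model.

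**The case against.** The strongest reply is that the choice of prognostic covariates for a secondary outcome belongs in the SAP. The protocol defers to a SAP approved by the steering committee, and 9.5 never says that only patient-reported outcomes may have baseline adjustment. Section 9.3.3 in fact goes further, to laboratory and dose outcomes. This stands to the extent that 9.5 does not forbid the covariate, and a SAP could add it. It does not remove the point: 9.5 sets a rule for all analyses, and a SAP written to that rule would leave out a collected predictor.

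The second reply is that the baseline item does not match the outcome. This stands. Table 1 counts day-case and inpatient admissions of any cause, while Table 2 defines the outcome by cardiovascular and infection diagnosis groups and lists other admissions separately. A reader might infer that the trial holds the outcome's own baseline value; it does not say so. The 6-month window appears only at the end of the Table 1 row, and Appendix 1 gives none for this item. Patients may enter just over 4 weeks after starting dialysis, so for some the look-back covers time before dialysis. Participants are not censored at transplant, so propensity may also change during follow-up. Each of these pushes the correlation below 1.

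Third, a reader might infer that substantial power is being given away. At an assumed rate ratio of 0.86, the full-sharing standard errors give power rising from 75% to 80%, 57% to 68% and 39% to 56% for k = 0.5, 1 and 2. The document does not support that reading. It contains no rate ratio of 0.86 and no power target for these outcomes. At its only attenuated effect, a hazard ratio of 0.79 for the composite, the same standard errors give 98% to 99%, 92% to 97% and 74% to 91%. With a correlation of 0.5, power at 0.86 rises by only 1-2 points.

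**Conclusion.** The point holds as a modest, free gain in efficiency. The hospitalisation models omit a relevant predictor that the trial already records, and precision on these secondary outcomes is somewhat lower than it need be. There is no bias, and the planned analysis is valid without the change.

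The documents cannot fix the size. At correlations of 0.5 to 0.7 the variance reduction is about 3-17%. About 38% is a ceiling that needs both a frailty variance of 2 and a propensity that is fully shared across causes and constant over follow-up. At a correlation of 0.3 the gain is only 1-3%. The direction was the same in every scenario run, so the case for the change does not depend on the exact figure.

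**What to change.** In 9.3.3 or 9.5, and in the SAP, add a sentence to this effect: the joint frailty models for cardiovascular and infection hospitalisations will also adjust for the number of hospital admissions in the 6 months before randomisation recorded at baseline, as a log-transformed count with a small constant added so that zero counts are defined. State whether the covariate enters the death component as well as the recurrent-event component, and confirm that the 6-month window applies to this item on the baseline form. Fix the wording before any results by arm are seen, so that the choice cannot look data-driven.

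The cost is one sentence and a simple rule for the few participants whose baseline count is missing, such as a missing-value indicator or simple imputation. No new data, visits or participant burden follow.

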#### **9.6 Interim analysis**

A formal interim analysis of all-cause mortality will be conducted using available data and discussed with the DMC. A one-sided  $p$ -value  $< 0.025$  for treatment differences (mortality (HD)  $<$  mortality (HDF)) would be considered a meaningful difference to be explored further. The analysis will take place half-way through the study although the exact timing of the analysis will be set by the DMC who will be guided by recruitment patterns and progress in obtaining permissions for relevant linkages.

|                                                                                                                                                                                                                                                                                                                                                                                             |                                                                                                                                                                                                                                                                                                                                                                                                                                                                                                                                                                              |
|---------------------------------------------------------------------------------------------------------------------------------------------------------------------------------------------------------------------------------------------------------------------------------------------------------------------------------------------------------------------------------------------|------------------------------------------------------------------------------------------------------------------------------------------------------------------------------------------------------------------------------------------------------------------------------------------------------------------------------------------------------------------------------------------------------------------------------------------------------------------------------------------------------------------------------------------------------------------------------|
|                                                                                                                                                                                                                                                                                                                                                                                             | 
1. The number of participants recruited is at least 85% of what would be expected if all 20 centres recruiting from the first day of the recruitment period at the expected rate (i.e. at least 388 of the required 456). This is regardless of the number of sites recruiting. OR
 
2. The number of sites recruiting is at least 85% of what would be expected (i.e. at least 17 of the required 20) AND the rate of participant recruitment per active site month is at least 85% of what would be expected (i.e. at least 3.4 of the required 3.8).
          |
|                                                                                                                                                                                                                                                                                                                                                                                             | 
1. The number of participants recruited is 60-84% of what would be expected were all 20 centres recruiting from the first day of the recruitment period at the expected rate (i.e. 274-387 of the required 456). This is regardless of the number of sites recruiting. OR
 
2. The number of sites recruiting is 60-84% of what would be expected (i.e. 12-16 of the required 20) AND the rate of participant recruitment per active site month is 60-84% of what would be expected (i.e. 2.3-3.3 of the required 3.8).
                                          |
|                                                                                                                                                                                                                                                                                                                                                                                             | 
1. The number of participants recruited is less than 60% of what would be expected were all 20 centres recruiting from the first day of the recruitment period at the expected rate (i.e. less than 273 of the required 456). This is regardless of the number of sites recruiting. AND
 
2. The number of sites recruiting is less than 60% of what would be expected (i.e. less than 11 of the required 20) AND the rate of participant recruitment per active site month is less than 60% of what would be expected (i.e. less than 2.2 of the required 3.8).
 |
| 
NOTE: The participant recruitment rate of 3.8 participants per active site month for the first six months of recruitment is slightly lower than the rate required across the whole trial, 4.3. This reflects the anticipated lower recruitment in the early months that the QRI work is intended to improve – 30% in months 1-4, increasing to 40% in months 5 - end of recruitment.
 |                                                                                                                                                                                                                                                                                                                                                                                                                                                                                                                                                                              |

In all cases, we will also report the percentage of HD patients that meet the eligibility criteria and then the percentage who consent to randomisation. To assess the generalisability of participants the characteristics of consenting participants and non-consenting and routine HD patients (from screening logs and UKRR data, respectively) will be compared. We will also report preliminary data on event rates observed in the trial population – death rates, cardiovascular and infection hospital admission rates, dropout rates, transfer to a centre not offering HDF, transfer to a different treatment modality such as peritoneal dialysis or transplantation – and how close these are to the assumptions made in the sample size calculation.

In the case of an amber result, a more detailed breakdown of site and participant recruitment would be provided, along with a review of event rates and crossover rates and a report from the QRI re the barriers to recruitment.

At the first DMC meeting, the committee will agree on its charter of operations and advise on the criteria for the need for interim analyses and adoption of formal stopping rules for efficacy or safety. The DMC will be responsible for assessing safety and efficacy; they will be responsible for

recommending stopping the trial at any time if there are significant safety or ethical issues. Judgements will be made at their discretion.

Any interim statistical analyses by study arm will be performed by the study statistician blinded to treatment allocation. They will report blinded data to the DMC who will have unblinded access to all data if they have concerns about the safety of the RCT and will discuss the results of the interim analyses with the TSC in a joint meeting. The TSC will then report to the central ethics committee.

A detailed statistical analysis plan will be developed for the approval of the TSC and will be finalised before any interim analyses are undertaken for the DMC.

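### The pilot progression table in section 9.6 gives 3.4 as 85% of 3.8 (it is 3.23), sets its lowest-row limits below the stated 60%, and leaves some results in no row

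*Protocol*

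**What the plan says.** Section 9.6 (Interim analysis) sets progression criteria for the first six months of recruitment. The targets are 456 participants, 20 sites and 3.8 participants per active site month.

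- **Top row.** Participants ("i.e. at least 388 of the required 456"), OR sites ("i.e. at least 17 of the required 20") AND a rate that "is at least 85% of what would be expected (i.e. at least 3.4 of the required 3.8".
- **Middle row.** Participants ("i.e. 274-387 of the required 456"), OR 12 to 16 sites AND a rate in the 60-84% band ("i.e. 2.3-3.3 of the required 3.8").
- **Lowest row.** Participants under 60% ("i.e. less than 273 of the required 456"), AND sites "less than 60% of what would be expected (i.e. less than 11 of the required 20", AND a rate "less than 60% of what would be expected (i.e. less than 2.2 of the required 3.8".

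The text after the table says what extra reporting follows an amber result. No rule covers a result that fits no row. The row names green and red are not visible in the text at hand. I infer them from the row order and the word amber, and use top, middle and lowest below.

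**The concern.** Each limit is printed as a percentage with its number beside it, and several pairs disagree. Someone applying the numbers would then grade the pilot differently from someone applying the percentages.

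The structure raises a second problem. The lowest row needs participants, sites and rate all to be low, while the middle row's second route admits only 12 to 16 sites. A trial with many open sites and poor recruitment at each can therefore miss every row.

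Feasibility of recruitment is a stated pilot objective (section 3.3), and this table is how it is judged. At stake is whether the pilot was graded as the percentages intend.

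**Working it through.** **Base figures.** Section 9.2 gives 4,104 eligible patients over 18 months, with participation of 30% in months 1-4 and 40% afterwards.

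- Eligible per month: 4,104 / 18 = 228.
- Six-month target: 228 × (4 × 0.30 + 2 × 0.40) = 456, as stated.
- Rate per site month: 456 / (20 × 6) = 3.8, as stated.
- Whole-trial rate: 1,550 / (20 × 18) = 4.31, stated as 4.3.

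The bases reproduce, so any fault lies in the limits.

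**Limits against their percentages.**

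| Quantity | 60% | 85% | Middle row starts | Top row starts | Lowest row |
|---|---|---|---|---|---|
| Participants (456) | 273.6 | 387.6 | 274 | 388 | <273 |
| Sites (20) | 12 | 17 | 12 | 17 | <11 |
| Rate (3.8) | 2.28 | 3.23 | 2.3 | **3.4** | <2.2 |

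The limits 388, 17, 274, 12 and 2.3 are right. The rest are not:

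- 3.4 / 3.8 = 89.5%. Rounding 3.23 up gives 3.3. An unrounded base of 3.75 to 3.85 gives 3.19 to 3.27. Using 4.3 as the base gives 3.66. None gives 3.4, which is 85% of 4.0.
- The middle-row ceiling is 3.3 / 3.8 = 86.8%, but 84% of 3.8 is 3.19. Read loosely as anything under 85%, the ceiling is still below 3.23.
- In the lowest row, 273 / 456 = 59.9%, 11 / 20 = 55% and 2.2 / 3.8 = 57.9%. All are under 60%, yet a row that excludes 273, 11 and 2.2 is labelled less than 60%.

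**Where the 3.4 bites.** It matters when at least 17 sites are open but too few active site months have accrued to reach 388.

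- 17 sites open throughout at 3.3 give 17 × 6 × 3.3 = 337 participants. Sites are at 85% and rate at 86.8%, so the percentages say top row. The printed limits say middle row.
- An illustrative staggered opening: 18 sites with 60 active site months at 3.3 give 198 participants. The percentages say top row (90% and 86.8%). As printed, no row fits: 198 < 274, 18 is outside 12-16, and 18 is not below 11.

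**Whether the rows are exhaustive.** Take half the per-site rate, 1.9, with sites open all six months.

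- 20 sites: 20 × 6 × 1.9 = 228 participants (50%). Not top (228 < 388; 1.9 < 3.4). Not middle (228 < 274; 20 is outside 12-16; 1.9 < 2.3). Not lowest (20 is not below 11).
- Every count from 11 to 20 sites gives the same answer. With 10 or fewer, the lowest row applies.
- Substituting exact percentages for the limits does not close the gap: 12 to 20 sites at 1.9 still fit no row.

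**Reach of the lowest row.** With sites open throughout it needs at most 10 sites below 2.2, so fewer than 10 × 6 × 2.2 = 132 participants, and 132 / 456 = 29%. Its 60% participant limit then never binds.

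**The case against.** Much can be said for the table.

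- **Not every rate of 3.23 to 3.39 is misgraded.** The 388-participant route stands alone. With 20 sites open throughout, 388 / 120 = 3.233, so a rate at 85% or above already reaches the top row in practice. A reader might infer that the wrong 3.4 always matters; it does not.
- **273 participants or 11 sites need not go ungraded.** 273 from 14 sites open throughout is 273 / (14 × 6) = 3.25 per site month, which is middle row by the second route. Eleven sites with 274 or more participants are middle row by the first.
- **Half of target does not always mean no verdict.** Half the per-site rate with 10 or fewer sites is lowest row. Half the total (228) from 12 to 16 sites open throughout is middle row, at rates from 3.2 down to 2.4.
- **Switching from OR to AND in the lowest row is not itself an error.** Joining its two numbered items by AND is the correct negation of an OR. The gap comes from requiring low sites AND low rate within the second item, together with the middle row's cap of 16 sites.
- **The period has probably passed.** The Trial Summary starts recruitment on 01/11/2017; this version is dated 3 May 2022.

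All five points stand. They narrow the reach and urgency of the problem. They do not make 3.4 equal to 85% of 3.8, or put 20 sites at 1.9 into a row.

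**Conclusion.** The point holds in a limited form. One top-row limit is wrong (3.4 for 3.23), as is the middle-row ceiling tied to it (3.3), and the three lowest-row limits sit below the 60% they are said to represent. Separately, the rows leave a gap that covers 11 to 20 sites at half the per-site rate over six months. That example, and the figure of 132 participants, assume that sites are open throughout; with staggered opening the counts change but the gap remains.

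A reader might infer that the lowest row is a stop rule. The text at hand does not support that: the row labels, and any actions printed with them, are not visible, and the only stated consequence is further reporting after an amber result. Nor does the error touch the sample size, alpha or any outcome analysis. It is a real fault in stated decision thresholds, with modest practical weight now.

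**What to change.** Restate the three rows so that exactly one applies to any result:

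- **Top:** at least 388 participants, OR (at least 17 sites AND a rate of at least 3.23).
- **Middle:** not top, and at least 274 participants OR (at least 12 sites AND a rate of at least 2.28), with no upper cap on sites or rate.
- **Lowest:** neither top nor middle.

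Removing the caps is essential. If the lowest row became the remainder while the middle row still stopped at 16 sites, 18 staggered sites with 72 active site months at 3.2 (about 230 participants) would fall into the lowest row, with sites at 90% and rate at 84% of target. Under the wording above they are middle row. The words 'not top' also settle an overlap in the printed table: 17 sites open throughout at 3.4 give 17 × 6 × 3.4 = 347 participants, which satisfies both the top and middle rows.

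The team should confirm one consequence. Fewer than 12 sites with fewer than 274 participants would be lowest row even at a good per-site rate; for example, 11 sites at 3.8 give 11 × 6 × 3.8 = 251.

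This changes the decision rule as well as the numbers, so it needs a short amendment or a documented correction. If the pilot decision has been taken, re-read it against these limits using the recorded participants, sites and active site months, and report whether the grade changes. No new data are needed.
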